## Abstract

**Background:**

Antiretroviral therapy (ART) for HIV-infected persons and pre-exposure prophylaxis (PrEP) for uninfected persons are extraordinarily effective strategies for HIV prevention. In Africa, the region which shoulders the highest HIV burden, HIV care is principally delivered through public health HIV care clinics, offering an existing platform to incorporate PrEP delivery and maximize ART and PrEP synergies. However, successfully bringing this integrated approach to scale requires an implementation science evaluation in public health settings.

**Methods:**

The Partners Scale Up Project is a prospective, pragmatic implementation evaluation, designed as a stepped-wedge, cluster-randomized trial, operating at 24 clinics in Kenya. In collaboration with the Kenya Ministry of Health, we are catalyzing scaled implementation of PrEP delivery integrated in HIV care clinics. The intervention package includes staff training, clinic streamlined access to PrEP commodity from the Kenya Medical Supply Authority, and ongoing intensive technical assistance to rigorously assess how PrEP delivery is implemented. PrEP service delivery including retention efforts are conducted by the clinic staff with no additional resources from the project. Guided by the RE-AIM (Reach, Effectiveness, Adoption, Implementation, Maintenance) framework and Consolidated Framework for Implementation Science Research, project progress and learning are documented through ongoing monitoring and process evaluations, including chart abstraction and individual and key informant interviews, to evaluate pragmatic rollout and understand barriers and facilitators for successful PrEP delivery in this setting. In this staged rollout design, each step provides data for both pre-implementation (baseline) and implementation periods, and we will compare time points across steps in the baseline versus implementation periods.

**Discussion:**

Cost-effective delivery models are urgently needed to maximize the public health impact of PrEP and ART. The Partners Scale Up Project will set the stage for full-scale PrEP implementation fully run and owned by the Kenya Ministry of Health. The work combines nationally sponsored PrEP delivery with technical support and implementation science from academic partners, defining a new but sustainable paradigm for public health collaboration.

**Trial registration:**

Registered with ClinicalTrials.gov on February 14, 2017:NCT03052010.

## Background

Heterosexual HIV-serodiscordant couples (i.e., in which one member is living with HIV and the other is uninfected) are common in high HIV prevalence African settings [1, 2]. Half of partners of persons living with HIV are uninfected, with women as likely as men to be the HIV-seropositive partner in a serodiscordant couple [3]. Serodiscordant couples are a priority population for implementing HIV prevention interventions, given their high risk [4–6], ability to be identified in generalized epidemic settings through couples HIV testing [5, 7–9], and support within the coupled relationship that facilitates prevention adherence [10, 11]. Pivotal clinical trials demonstrated very high efficacy for HIV prevention strategies in couples [12], including antiretroviral therapy (ART) for HIV-infected partners [13] and pre-exposure prophylaxis (PrEP) for HIV-uninfected partners [12]. A pragmatic, integrated approach to providing ART and PrEP, with ART promoted for the HIV-infected partner and PrEP offered to the uninfected partner until 6 months after ART initiation, or until the HIV-positive partner achieves virologic suppression (a strategy called “PrEP as a bridge to ART”), resulted in near elimination of HIV transmission in a demonstration project among HIV-serodiscordant couples [14].

In September 2015, the World Health Organization (WHO) recommended ART for all HIV-diagnosed persons and PrEP for persons at high risk of HIV acquisition [15]. In July 2016, the Ministry of Health (MOH) in Kenya released guidelines which recommended initiation of ART for all HIV-infected persons irrespective of CD4 count and PrEP for HIV-uninfected persons with substantial ongoing risk of HIV infection [16]. In the guidelines, priority persons for HIV prevention include HIV-uninfected members of serodiscordant couples, particularly those couples in which the HIV-infected partner is not yet taking ART or has not achieved viral suppression on ART.

The Partners Demonstration Project [14] which showed near elimination of HIV transmission using integrated PrEP as a bridge to ART strategy was an important initial step for advancing PrEP and ART for couples from clinical trials to delivery settings. However, translating this success to scale requires effective implementation to achieve public health impact. HIV care in Kenya is principally delivered through public health HIV care clinics, offering an existing platform to incorporate PrEP delivery. Using a stepped-wedge trial design to randomly assign HIV care clinics to scaled initiation of PrEP integrated into HIV care for couples, the RE-AIM (Reach, Effectiveness, Adoption, Implementation, Maintenance) framework [17] and the Consolidated Framework for Implementation Science Research (CFIR) [18] are applied to guide rollout of integrated PrEP for serodiscordant couples in Kenya (The Partners Scale up Project). Here, we describe the design and the application of the RE-AIM and CFIR frameworks for this project.

## Methods

### Goals and specific aims

The overall goal of the Partners Scale Up Project is to serve as a catalyst for expansion of PrEP delivery in public HIV clinics in Kenya and to document best practices for PrEP delivery. The specific aims are:Facilitate delivery of PrEP integrated into ART care for HIV-serodiscordant couples at scale in public HIV care centers in Kenya and evaluate program impact;Assess facilitators and barriers to (a) implementation of PrEP within ART delivery settings and (b) optimized PrEP adherence in public health context with limited measurement capacity;Determine efficiency, cost, and cost-effectiveness of integrated PrEP and ART when delivered in public health clinics; andDevelop operational tools that will expand and support delivery of PrEP at scale and secure buy-in from relevant stakeholders to ensure delivery continues to scale up at the national level.

### Design

The Partners Scale Up Project is a prospective, pragmatic implementation evaluation, designed as a stepped-wedge, cluster-randomized trial, operating at 24 clinics in Kenya. In this design, each step provides data for both pre-implementation (baseline) and implementation periods, and data analysis proceeds by comparing time points across steps in baseline versus implementation periods. In collaboration with the Kenya MOH, PrEP delivery was introduced in public health HIV clinics in a staged fashion, with ongoing intensive technical assistance and monitoring and evaluation conducted to rigorously assess how PrEP delivery is being implemented. PrEP provision including behavior risk assessment, demand creation, and retention activities are conducted by public health staff, with no additional resources provided by the project team. Project progress and learning are documented through ongoing monitoring and process evaluations, including chart abstraction and individual and key informant interviews, to evaluate pragmatic rollout and understand barriers and facilitators for successful PrEP delivery in this setting.

### Context

HIV-uninfected individuals with HIV-positive sexual partners became eligible for PrEP per the Kenya national guidelines on use of antiretroviral drugs for treatment and prevention of HIV released in 2016 [16]. A national PrEP implementation framework and service provider toolkit was developed by the Kenya MOH [19], with contribution from the Partners Scale Up Project team. PrEP rollout nationally in Kenya was officially launched in May 2017 and is expanding at a variety of care centers, aimed at providing HIV prevention to key populations [19]. Kenya guidelines specifically recommend PrEP for HIV-uninfected members of HIV-serodiscordant couples until the HIV-infected partner achieves viral suppression with effective ART, in serodiscordant couples desiring safer conception or if otherwise meeting behavioral criteria for individuals to receive PrEP (e.g., additional sexual partners of positive or unknown HIV serostatus, sex work).

### Setting and facility selection

The Partners Scale Up Project is being implemented in 24 Comprehensive Care Clinics (the term used for public health HIV clinics) in two geographical regions of Kenya: Central and Nairobi regions, herein referred to as Central (Kiambu, Kirinyaga, Murang’a, Nairobi, Nyeri counties) and Nyanza, herein referred to as Western (Homa Bay, Kisumu, Migori, Siaya counties). High-volume clinics with established ART programs were identified. Final participating clinics were then selected in consultation with MOH/National AIDS & STI Control Programme (NASCOP) and county health authorities prior to project initiation and reflect the Kenya Ministry of Health HIV priority areas based on HIV prevalence, diversity, and health care settings (Fig. 1). Lessons learnt from the pioneering 24 clinics will be used to inform dissemination of PrEP implementation nationally, including in regions where the project did not initially operate.

**Fig. 1 Fig1:**
[figure not shown]
Clinical settings. Counties in Kenya with high and medium HIV incidence

### Randomization

Beginning February 2017, we implemented a stepped-wedge trial design to randomly assign 24 HIV care clinics to scaled implementation of PrEP integrated in HIV clinics for couples. During the project pre-implementation period, PrEP was sanctioned as part of  standard of care by the Kenya national guidelines but there were no systematic approaches in place for implementation in clinical settings. The project intervention is to be a catalytic force to integrate PrEP delivery in public HIV clinics nationally and the intervention package includes staff training, clinic streamlined access to PrEP commodity from Kenya Medical Supply Authority (KEMSA), and ongoing PrEP technical assistance. Prior to randomization, the 24 clinics were stratified by region (12 Central, 12 Western), and each clinic was randomized to the order in which it would start implementing PrEP delivery. The randomization process was conducted at a public event attended by national and county health representatives. Facility leadership picked the order of initiation from an opaque bag containing numbered balls labeled from 1 to 12. Following randomization, the implementation was rolled out in groups of two to four clinics (Fig. 2). Program indicators to measure number of serodiscordant couples newly identified through couples HIV testing, number of HIV-uninfected individuals initiating PrEP, and number of HIV-infected individuals newly initiating ART are obtained monthly from all participating clinics starting 1 month prior to the project initiation.

**Fig. 2 Fig2:**
[figure not shown]
Schema for the cluster-randomized stepped-wedge design

### Sample size

Using 24 clinics with a baseline period, two to four clinics implementing at each step, and 50 at-risk HIV-uninfected persons initiating PrEP per clinic every 6 months (200 couples on average per site overall, 4800 total), the trial is estimated to have > 90% power to detect a minimum 10% difference in the number of at-risk HIV-uninfected individuals initiating PrEP (defined below as Reach) after implementing the intervention, with a two-sided alpha of 0.05. This difference was conservatively chosen, recognizing that as interventions move to scale their impact is often diminished (a “voltage drop” along successive steps of an implementation cascade [20]).

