### Analysis

#### Quantitative data

The primary outcome will be the number of at-risk persons initiated on PrEP (Reach). The number initiated on PrEP during baseline period (i.e., pre-implementation period) will be compared with that across the implementation observation periods (exposed or intervention period). Generalized linear mixed models, to estimate the primary intervention effect where both differences observed within steps (between randomized clinics) and changes observed within each clinic as it implements the intervention (within clusters), contribute information. A random effect for each clinic, a fixed effect for each time step, and the fixed intervention effect will be fitted for each time period. Categorical variables will be detailed in tables, and continuous measures will be summarized using means and standard deviations or medians and ranges, as appropriate. *T* tests will be used to detect differences in mean levels of continuous variables and chi-square tests for dichotomous variables.

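### On the stated count outcome and mixed model, 4,800 initiations do not give the > 90% power claimed for a 10% relative increase; plausible settings give about 25% to 51%.

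*Protocol article*

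**What the plan says.** The Sample size section of the protocol article fixes these inputs:

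- Layout: "Using 24 clinics with a baseline period, two to four clinics implementing at each step".
- Event rate: "50 at-risk HIV-uninfected persons initiating PrEP per clinic every 6 months".
- Volume: "200 couples on average per site overall, 4800 total".
- Test level: "with a two-sided alpha of 0.05".
- Claim: "the trial is estimated to have > 90% power to detect a minimum 10% difference in the number of at-risk HIV-uninfected individuals" starting PrEP.

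The Quantitative data section names the endpoint: "The primary outcome will be the number of at-risk persons initiated on PrEP (Reach" is its label. It specifies a generalized linear mixed model containing "A random effect for each clinic, a fixed effect for each time step, and the fixed intervention effect". Table 1 and the Outcome measures section also give the project's Reach measure as a number of persons, and no denominator is attached to the power statement.

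**The concern.** In a stepped-wedge trial, fitting an effect for every time step removes the part of the before-after contrast that cannot be separated from calendar time. Clinic effects take out more. What remains is much less information than a plain comparison of exposed and unexposed totals would suggest. With 4,800 events, a 10% difference is close to the limit of what even the plain comparison can detect, so a claim of > 90% under the full model needed checking.

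The stake is interpretation. A reader who accepts the printed power would take a null or imprecise estimate as evidence against a 10% gain, although the design would detect such a gain about half the time at best under ordinary assumptions.

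**Working it through.** **Inputs from the article.** There are 24 clinics in groups of two to four, so 6 to 12 steps. The rate is 50 initiations per clinic per 6 months, or 8.33 per month. With 200 per clinic, observation lasts 200/50 × 6 = 24 months, and 24 × 200 = 4,800. Alpha is 0.05 two-sided. The 10% is read as a rate ratio of 1.10, with ln(1.10) = 0.0953.

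**Assumptions, because the text does not give them.** Counts are Poisson. The between-clinic SD on the log scale is 0 to 0.5. Steps run from one month up to evenly spaced over 24 months. The step schema is in a figure that is not visible in the copy reviewed.

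**1. Trying to reproduce > 90%.** Take two independent Poisson totals of 2,400 each, with no clinic or time effect:

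- SE(log ratio) = √(1/2400 + 1/2400) = 0.0289
- 0.0953/0.0289 = 3.30
- power = Φ(3.30 − 1.96) = Φ(1.34) = 91.0%

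With 2,400 v 2,640 it is 92.2%. This comparison also needs half of all clinic-time to be baseline. With 25% baseline it gives 82%, and with 10% it gives 51%.

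**2. The planned model.** Generalized least squares on the log scale, with cell variance 1/μ (μ is the expected count, 10% higher once exposed), a fixed effect per period and a random clinic intercept. Power = Φ(0.0953/SE − 1.96). With clinic SD 0.3:

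| Rollout | Steps | SE | Power |
|---|---|---|---|
| One-month steps, one baseline month | 6 | 0.0745 | 25% |
| | 8 | 0.0655 | 31% |
| | 12 | 0.0559 | 40% |
| One baseline period plus equal steps over 24 months | 6 | 0.0491 | 49% |
| | 8 | 0.0485 | 50% |
| | 12 | 0.0481 | 51% |

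For example, with 8 equal steps, 0.0953/0.0485 = 1.965 and Φ(0.005) = 50%. With clinic SD 0.5 the ranges are 25-40% and 48-50%. Two- and three-month steps fall between or close to these values (39-51%).

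Fast rollout costs power because once all clinics have crossed over there is no concurrent comparison. With six one-month steps after one baseline month, every clinic is exposed from month 7, so 18 of 24 months have no unexposed clinic.

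**3. Simulation.** Poisson data with clinic SD 0.3, 8 steps and 600 runs per setting gave 29%, 46% and 50% for steps of one, two and three months. Type I error was 5%.

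**4. How far the assumptions can move this.**

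- No between-clinic variation: 27% to 86% across the rollouts tried, and 71-75% with even steps.
- Clinic SD 0.1: 26% to 64%.
- Added clinic-by-period SD of 0.1, 0.2 or 0.3 (8 even steps, clinic SD 0.3): 43%, 30% and 21%.
- 58 months at the same rate (24 × 58 × 8.33 = 11,600 initiations), clinic SD 0.3: at most about 86%.

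**5. Difference detectable with 90% power at 4,800.** Ratio = exp[(1.96 + 1.28) × SE]. The smallest SE, 0.0481, gives 1.17. The largest, 0.0745, gives 1.27. These hold for Poisson variation only. With clinic-by-period SD 0.3 and 8 even steps, SE is 0.083 and the ratio is about 1.31.

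**The case against.** **The inputs are not shown.** Step length and clinic variance are absent from the text, and a condensed article may leave them to the full protocol. This stands against quoting any single replacement figure. A reader might take 25-50% as a property of the trial, but it is conditional on the clinic SD and on 24 months. It does not rescue > 90%, which was not reached in any count-based setting tried with 4,800 initiations.

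**Other readings do reach 90%.** A difference of ten percentage points in a proportion gives about 98-100%, and the general RE-AIM definition of Reach in Table 1 mentions proportions. But the project's own measure is a number, and no denominator is given. Reading 50 as the count per step rather than per 6 months gives about 71-94% at clinic SD 0.3 or with fixed clinic effects. That needs 8,400 to 15,600 initiations, which contradicts the 4,800 total.

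**The authors' method.** A reader might infer from the 91% match that the figure came from comparing two totals of 2,400. The article shows no formula, so this is unknown.

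**The true effect may be much larger than 10%.** The Randomization section says no systematic approach to delivery existed before implementation, and the Sample size section calls the 10% a conservative choice. With Poisson variation only, a ratio of 1.3 has 93% power or more and 1.5 has essentially 100%. This limits the practical harm. The printed claim is nevertheless about 10%, and few baseline initiations would leave less information than assumed here.

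**Conclusion.** The point holds for a 10% relative increase in the count of initiations, analysed with the stated model. Power is about 25-40% with one-month steps and 48-51% with evenly spaced steps, given Poisson counts, 24 months and a between-clinic log SD of at least 0.3. Values clearly above one half require clinics with nearly identical initiation rates, which is hard to assume across the counties and varied settings listed under Setting and facility selection. Even with no clinic variation the result stays below 90%, and clinic-by-period variation lowers it.

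That the printed figure is not delivered on the stated outcome is firm. The exact replacement depends on step lengths and variances that only the investigators can supply. It does not follow that the trial would miss its effect: at the upper end of the range a true 10% gain is an even chance, and a substantially larger gain could well be detected.

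**What to change.** Recompute power under the model in the Quantitative data section, using the actual step lengths and stated values for between-clinic and clinic-by-period variation. State that the 10% is a relative change in the number initiating PrEP. Then restate one of two things: the power at 10%, or the difference detectable with 90% power. With Poisson variation only, the latter is about 17% for evenly spaced steps, rising to about 27% for the fastest rollout, and it is larger with clinic-by-period variation. A best-case evenly spaced figure should not be printed unless the rollout was in fact evenly spaced.

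The cost is a rewritten sample-size paragraph and a less favourable stated figure. Enrolment, randomization and conduct do not change.

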### Project activities

PrEP has regulatory and normative guidance sanction in Kenya and has been defined as part of standard care, in part based on a series of clinical trials and implementation studies done in Kenyan populations [12, 21–29]. Thus, the intention of the Partners Scale Up Project is to study the process of integrating PrEP services for HIV-serodiscordant couples in HIV clinics and not the PrEP medication itself. PrEP delivery activities are fully conducted by MOH staff in accordance with Kenyan national guidelines; project staff conduct technical assistance and monitoring and evaluation activities to characterize the implementation processes, define facilitators and barriers, and measure uptake, adherence, and costs. The components of the implementation (intervention) package (i.e., activities conducted by the project) include (1) health care provider training on clinical delivery of integrated PrEP and ART for couples, (2) development of operational tools for PrEP delivery, (3) monitoring and evaluation and implementation process evaluation, (4) economic evaluations, and (5) stakeholder and community engagement.*Health care provider training*: Training health care providers is an essential component of implementation of a new clinical strategy in a public health setting. Health providers from each clinic were trained using a 2-day case-based interactive curriculum, developed in conjunction with the Kenya MOH [19]. Content specific to HIV-serodiscordant couples was added, including topics on HIV treatment as prevention and providing couples-based care, with the goal of equipping health providers with the knowledge and skills to provide PrEP to the HIV-uninfected person in a HIV-serodiscordant partnership. A standardized pre- and post-test about PrEP and antiretroviral-based HIV prevention was used to assess knowledge before and after the training. Clinics began PrEP delivery after the training following the randomization order.*Development of PrEP delivery operational tools*: The project has developed operational tools to expand and support delivery of PrEP at scale including a clinical encounter form for documenting PrEP visits in clinics that has been adopted by the Kenya MOH to be the service delivery tool for PrEP implementation for all populations in Kenya (i.e., not only couples and not only at the 24 clinics in this project). The form captures demographic information and ongoing evaluation for behavioral HIV risk factors, HIV testing and other laboratory monitoring, PrEP pharmacy dispensing, adherence self-rating, and side effects.*Monitoring and evaluation and implementation process evaluation*: The Partners Scale Up Project is conducting rigorous process evaluation activities to monitor how effectively PrEP delivery is implemented, including mixed-methods assessments to explore and gain deep understanding of the process of PrEP implementation and contextual influences on implementation and outcomes in clinical settings. Domains defined in the RE-AIM implementation science framework [17] (Table 1) are used to investigate the extent to which PrEP is delivered to at-risk persons (Reach), important clinical or behavioral outcomes (Effectiveness), uptake by clinics and patients and provider acceptance (Adoption), consistency of implementation (Implementation), and contextual factors that influence institutionalization of PrEP delivery over time (Maintenance). Project activities for monitoring and evaluation include ongoing technical assistance, clinical data abstraction, objective measurement of PrEP adherence, and qualitative interviews with PrEP users, health providers, and managers.

**Table 1 Tab1:** Application of the RE-AIM framework to evaluate the programmatic scale-up of PrEP integrated into public health HIV clinics

Domain	Original RE-AIM definition	Measurement level	Project-specific outcome measures
Reach	Reach is the absolute number, proportion, and representativeness of individuals who are willing to participate in a given initiative	Individual	▪ Number of at-risk persons initiated on PrEP ▪ Demographic and behavioral characteristics of PrEP initiators
		Clinic	▪ Characteristics of implementing clinics ▪ Demand creation strategies ▪ Retention strategies
Effectiveness	The impact of an intervention on outcomes, including potential negative effects, quality of life, and economic outcomes.	Individual	▪ Incident HIV infection among PrEP users ▪ Proportion of random blood samples with detectable tenofovir levels ▪ Frequency of adverse clinical events related to PrEP use
		Program	▪ Cost and cost-effectiveness outcomes: unit cost, HIV infections averted, ICER, DALYS
Adoption	Absolute number, proportion, and representativeness of settings and intervention agents who are willing to initiate a program	Individual	▪ PrEP continuation rates ▪ Barriers/facilitators for PrEP initiation and use
		Clinic	▪ Number of clinics implementing PrEP in HIV clinics ▪ Number of MOH clinical staff trained on delivering PrEP ▪ % of trained MOH staff scoring > 80% on post-test ▪ % of trained clinical staff who delivered PrEP at least once ▪ Internal and external factors influencing PrEP implementation
Implementation	The intervention agents’ fidelity to the various elements of an intervention’s protocol	Clinic	▪ Number and % of users appropriately initiated on PrEP ▪ % of trained staff who delivered PrEP at least once ▪ Clinic innovations and adaptions ▪ Consistency of implementation across staff
Maintenance	The extent to which a program or policy becomes institutionalized or part of the routine organizational practice	Individual	▪ 6-month PrEP continuation rates
		Clinic	▪ Number of clinics implementing PrEP in HIV clinics ▪ Number of clinics that have integrated PrEP delivery in HIV clinics as an on-going part of their regular activities (i.e., have PrEP goals and targets, PrEP in service charter, routine health talks, regular staff training, implementation, PrEP data for monitoring and evaluation) ▪ Internal and external factors influencing PrEP implementation ▪ Number of clinics regularly completing PrEP M & E tools and report PrEP indicators to MOH
		National program	▪ PrEP delivery in HIV clinic continuing as part of Kenya MOH program ▪ M & E tools supplied to clinics ▪ PrEP indicators defined expected

